#### Masking

Whereas participants are informed about which treatment condition they are allocated to, the interviewers conducting the video interviews and thus assessing the outcomes of the study are blind to the participants’ group allocations. At the beginning of each interview, the participant is reminded to remember the confidential nature of their allocation and not to tell the interviewer which treatment they are receiving.

### Interventions

#### Bouldering psychotherapy (BPT)

The bouldering intervention is a combination of bouldering and psychotherapy and consists of 10 consecutive sessions. Unlike rock climbing, bouldering is defined as climbing to moderate heights (up to about 3 m) without the use of ropes or harnesses. Potential falls or jumps are protected by thick mats. The wide range of difficulty levels (usually indicated by different colors) makes it possible for people with different levels of fitness to boulder together in the same group. The sessions are 2 h each, taking place in a bouldering gym in Erlangen every week in the late afternoon. Each group consists of approximately 10 participants who are supervised by a team of two climbing therapists. All of the three climbing therapists are psychotherapists with bouldering and rock-climbing experience, and at least one member of the team has received advanced training form the German Alpine association, including safety requirements in bouldering.

The contextual focus of each session is on a specific psychological topic considered to be relevant in the development and maintenance of depression (see Table 2).

**Table 2 Tab2:** Overview of the bouldering therapy sessions

**Session**	**Topic**
1	Introduction to bouldering and mindfulness
2	Body awareness and the body’s center of gravity
3	Dealing with boundaries
4	Expectations and aspirations
5	Self-efficacy, achievement, and pride
6	Self-worth
7	Fear and confidence I
8	Fear and confidence II
9	Social relationships
10	Closing: problem solving, reflection on lessons learned, transfer to everyday life, and farewell

In the BPT sessions, therapists follow a BPT manual [56] that includes a fixed schedule for each session to provide a standardized implementation of the BPT (www.bouldering-psychotherapy.com). All of the 10 sessions consist of three main parts: introduction (about 20 min), action phase (about 75 min), and closing (about 25 min). The introduction phase is held in a room that is separate from the bouldering hall (e.g., the yoga room) and begins with a mindfulness exercise (e.g., breathing meditation) to help participants settle in and focus their attention on the present moment. The exercise is followed by a presentation of the session’s topic and psychoeducation (e.g., function and body signals of anxiety). At the end of introduction phase, participants engage in a brief exchange about their experiences with the topic. Afterwards, the group is divided into two smaller groups that are each supervised by one therapist from that point on. During the action phase, participants complete one or two topic-related bouldering exercises that are supposed to evoke underlying emotions (e.g., anxiety), uncover participants’ characteristic patterns (e.g., avoidance), and enable them to engage in new experiences (e.g., exposition: bouldering blindfolded) with the support of the therapists. This phase takes place in the bouldering hall. After completing these exercises, the remaining time is used for free bouldering during which everyone works on their individual “projects” while being supported by the therapists. For the closing phase, the two groups reunite in the enclosed room, talk about their experiences during the bouldering exercises, and develop ideas about how to integrate the lessons they learned into their everyday lives. All sessions end with a body-related relaxation exercise.

#### Mental model therapy (MMT)

Mental model therapy is based on the assumption that internalized cognitive distortions, biased decision making, and false assumptions lead to stress and reduced self-esteem. The goal of MMT is to trace these cognitive errors and replace them with more useful mental models (see Table 3). The central mental model is the Eisenhower principle, which helps prioritize what is really important: By distinguishing between important versus less important activities crossed with urgent versus not urgent activities (four quadrants), participants learn to overcome the natural tendency to focus on unimportant urgent tasks and instead learn to engage in long-term activities that are crucial for their well-being. MMT is expected to reduce stress and depressive symptoms and to have a preventive effect on future mental disorders by promoting a sense of coherence, resilience, and resources. The intervention consists of 10 consecutive, weekly 2-h sessions that take place in groups of about 10 participants in the psychiatric unit at the University Hospital Erlangen. Each group is led by a team of two therapists (out of three different therapists) who were specially trained in manualized MMT before the intervention. Equivalent to the qualification of the BPT therapists, all MMT therapists are psychiatrists, psychotherapists, or psychologists who are in the process of completing their psychotherapy hours (according to German law, psychotherapists must have an MSc degree in psychology plus an additional 4200 h of additional education as a psychotherapist). All therapists are experienced in the treatment of depression. Comparable to the BPT intervention, each session focuses on a specific psychological topic concerning cognitive distortions and misconceptions (see Table 3).

**Table 3 Tab3:** Overview of the MMT sessions

**Session**	**Topic**
1	Introduction, Eisenhower principle
2	Habits & Pareto principle
3	Balance model & Ivy-Lee Method
4	Solomon paradox [57] & Focusing illusion
5	Saying no & Mental models
6	Active language & Confirmation bias [58]
7	Compass of life & Sunk cost fallacy [59]
8	Hindsight bias [60] & Decisions
9	Radical acceptance [61] & Occam’s razor [62]
10	Closing: Reflection and transfer to everyday life, farewell

In the MMT sessions, therapists follow a manual that describes how to structure each session to ensure a standardized implementation. All 10 sessions consist of the following phases: a starting phase (about 20 min), one or two active phases with a break of 10 min (about 85 min), and a closing phase (about 15 min). The starting phase begins with a brief round in which everyone shares their current state of mind, followed by a discussion about the last session’s homework and difficulties that may have occurred. In order to create a more personal atmosphere and to give everyone the opportunity to exchange ideas, the participants will be divided into smaller groups with rotating members for the first phase. During the active phase(s), the small groups are reunited so that they can provide input on the sessions’ topics before they are divided into smaller groups again for a topic-related intervention. The intervention is followed by a discussion in the whole group again about participants’ experiences and difficulties. Some interventions do not require teamwork and are carried out as individual work. After the active phase(s), the session ends with a closing phase consisting of a homework assignment and everyone sharing their take-home message.

#### Control group (CG)

The CG receives no study-specific additional therapy during the intervention phase but is free to undergo all established psychotherapeutic and psychiatric treatment options and therefor represent treatment as usual in the German Health Care System. Participants allocated to the CG are given city vouchers (that can be redeemed in numerous regional shops and locations) or free passes to the local bouldering hall after completing measurement times t1 and t2. If interested, they are also offered preferential admission to the outpatient BPT group at Erlangen University Hospital after t1.

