**Methods:**

The study is being conducted as a randomized controlled intervention trial. Adult participants with unipolar depression are being randomized into three groups (BPT, MMT, or CG), and the first two groups are undergoing a 10-week treatment phase. CG follows their individual standard treatment as usual. A priori power analysis revealed that about 120 people should be included to capture a moderate effect. The primary outcome of the study is depression rated with the Montgomery and Asberg Depression Rating Scale (MADRS) before (t0), directly after (t1), and 12 months after the intervention phase (t2). Data are being collected via questionnaires, computer-assisted video interviews, and physical examinations. The primary hypotheses will be statistically analyzed by mixed model ANOVAs to compare the three groups over time. For secondary outcomes, further multivariate methods (e.g., mixed model ANOVAs and regression analyses) will be conducted. Qualitative data will be evaluated on the basis of the qualitative thematic analysis.

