### Study design and setting

The study was designed as a randomized, controlled, interventional, prospective, longitudinal, assessor-blinded study with three arms (BPT, MMT, CG). The overall start date was on October 1, 2021. Recruitment began on March 29, 2022, and will continue through February 28, 2023, in the Erlangen/Nuremberg/Fuerth region, a metropolitan region of three cities. After passing a diagnostic screening interview, participants are randomly assigned to one of the IGs (BPT or MMT) or the CG. Both IGs consist of 10 weekly 2-h sessions with a maximum of 11 participants and are each led by two therapists. After the end of the intervention phase, participants in the CG will be offered preferential admission to an outpatient BPT group at University Hospital Erlangen. MMT will be directly evaluated in an RCT design because many of its single components are well-established and well-investigated cognitive distortions. As it is very unlikely that the novel long-term focus on transforming thinking errors into appropriate goal-oriented thinking and action could lead to significant side effects, a previous open trial was not deemed mandatory. In all four consecutive waves of the study, the interventions are taking place simultaneously. To collect the data, structured video interviews are being conducted at baseline before the onset of therapy (t0), after the intervention (t1), and 12 months after the end of the intervention (t2). In addition to the interviews, participants are required to complete a series of questionnaires online (at t0, t1, and t2) and to undergo a physical examination with blood sampling (at t0 and t1 at about the same time of day). All procedures were approved by the Friedrich-Alexander-Universität Erlangen-Nürnberg Ethics Committee (Ref. 21-332-B) on December 13, 2021. The SPIRIT participant timeline is shown in Fig. 1, and the SPIRIT checklist is provided as an Additional file [51]. Trial Registration Data are presented in Table 1 (ISRCTN12347878, Registration date: March 28, 2022, registered prospectively).

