### Sample size estimation

ITT sample size was calculated on the basis of the authors’ previous experiences with BPT. Both studies on the effectiveness of BPT showed a moderate effect size (Cohen’s *d*s of 0.55 to 0.77) on depression severity [24, 25]. On the basis of effect sizes for CBT [9], comparable effect sizes are expected for MMT. Thus, an a priori power analysis to identify a moderate effect of *f* ≥ 0.295 was computed with the statistical program *G*Power* version 3.1.9.7. The calculations for the mixed ANOVA with two repeated measures as within-subjects factors and three groups as between-subjects factors and a group × time interaction revealed a total sample size of 114 participants. Power was set at 80%, *α* = .05, a correlation between repeated measurements of .50, and a nonsphericity correction of 1. To create three equal-sized groups each consisting of 10 participants across the four waves of recruitment, we planned to recruit a total of 120 participants, resulting in a total of 40 participants per group.

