#### Quantitative measurements

The primary hypothesis will be tested via mixed model ANOVAs with which potential interactions between time and group can be detected. To test the first and second hypotheses, a mixed model ANOVA with the between-subjects factor group and the within-subjects factor time as well as the group × time interaction will be calculated. Additionally, multiple regression analyses will be calculated to control for the effects of possible confounding variables (e.g., demographics, additional therapeutic treatments, such as antidepressant medication and psychotherapy).

Secondary outcome variables will be tested in an exploratory fashion with mixed model ANOVAs.

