The strengths of the present study are the randomization, the mixed methods approach, the naturalistic design with very few exclusion criteria, and the longitudinal character of the study with a long follow-up period of 1 year after the end of treatment. The use of manualized treatments in a naturalistic setting will contribute to the high internal and external validity of the study. The inclusion and exclusion criteria are being assessed via diagnostic screening interviews in contrast to self-report assessments. Additionally, the severity of depressive symptomatology as the primary outcome is being collected by blinded interviewers, and the interrater reliability is being assessed. A methodological limitation might be a possible selection bias due to people choosing to participate because they are interested in the therapies. Therefore, group preference is being taken into account during randomization, and it will be possible to compare subgroups with respect to their group preference. Also, the selection of a specific therapy on the basis of interest in the intervention is naturalistic and will hence contribute to higher external validity. Another limitation is the fact that the psychotherapeutic interventions themselves cannot be blinded. Furthermore, the clinical heterogeneity of the sample could lead to a reduction in effect sizes but would also strengthen external validity. As participants are free to continue with or begin other individual treatments during the study, possible confounding effects due to simultaneous interventions cannot be ruled out. However, ongoing and new treatments as well as changes in treatment plans during the study will be assessed at all measurement points, and the data will be considered in the analyses.

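### The primary time point is not fixed consistently, and because controls are offered BPT after t1, the 12-month contrast is not a comparison with treatment as usual

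*Protocol article*

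**What the plan says.** - **Primary outcome and test.** The abstract gives the primary outcome as MADRS "before (t0), directly after (t1), and 12 months after the intervention phase (t2"), and adds: "The primary hypotheses will be statistically analyzed by mixed model ANOVAs to compare the three groups over time".
- **Analysis section (Quantitative measurements).** For both hypotheses, "a mixed model ANOVA with the between-subjects factor group and the within-subjects factor time as well as the group × time interaction will be calculated". The levels of time are not given.
- **Sample size estimation.** "The calculations for the mixed ANOVA with two repeated measures as within-subjects factors", three groups, f = 0.295, α = .05, 80% power and a correlation of .50 give 114 participants, raised to 120 (40 per group).
- **Aim and hypotheses.** The aim is superiority of BPT and of MMT over a control group on treatment as usual. Neither hypothesis names a time point, and neither does the primary outcome entry in Table 1.
- **What controls are offered.** Study design and setting says that after the intervention phase "participants in the CG will be offered preferential admission to an outpatient BPT group at University Hospital Erlangen". The Control group section places this after t1: "If interested, they are also offered preferential admission to the outpatient BPT group at Erlangen University Hospital after t1". As a reward, controls receive city vouchers or "free passes to the local bouldering hall after completing measurement times t1 and t2".
- **Claimed strength.** The Discussion lists "the longitudinal character of the study with a long follow-up period of 1 year after the end of treatment".

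**The concern.** Read with the abstract, the primary interaction covers three occasions. Between the second and third, the trial itself offers controls one of the two treatments under test. At t2, hypothesis I then compares BPT now with usual care plus optional BPT later. Hypothesis II compares MMT with a mixture of usual care and BPT. Neither is the comparison with treatment as usual that the aim describes.

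Read with the sample size section, the primary test covers t0 and t1 only, and its contrast is not touched by the offer. The two readings are different primary tests with different meanings, and the article does not choose between them. If the choice stays open until t2 data are seen, a significant interaction could be reported as superiority over usual care when the three-occasion pattern does not show that.

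**Working it through.** **1. Reproduce the stated sample size.** Inputs from Sample size estimation: f = 0.295, three groups, two measures, α = .05. Interaction F test with df = 2 and N − 3, and λ = f²N:
- N = 114: λ = 0.295² × 114 = 9.92, power 80.1%. This matches the stated 114.
- N = 120: λ = 0.295² × 120 = 10.44, power 82.3%.

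In this form the correlation does not enter separately. The form λ = f²Nm/(1 − ρ) would give N = 33, so it is not the one behind the stated figure. The stated total is thus a two-occasion calculation.

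**2. Size of the t2 contrast.** Assume that a share p of controls takes up BPT after t1 and gains its full effect d by t2, and that both active arms keep d. The expected t2 difference from control is (1 − p)d. The protocol gives no uptake figure, so p is an assumption.

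| d | p = 0 | p = 25% | p = 50% | p = 75% |
|---|---|---|---|---|
| 0.55 | 0.55 | 0.41 | 0.28 | 0.14 |
| 0.59 | 0.59 | 0.44 | 0.30 | 0.15 |
| 0.77 | 0.77 | 0.58 | 0.39 | 0.19 |

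The values 0.55 and 0.77 are the protocol's range for earlier BPT trials. The value 0.59 is 2 × 0.295 and is an assumption of this check, not a figure in the protocol.

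**3. What the three-occasion omnibus test can see.** Assume 40 per arm, SD 1, ρ = .50, both active arms equal, and a difference from control of 0 at t0, d at t1 and r·d at t2, where r = 1 − p.
- Group part: S = (2/3)d². At d = 0.59, S = 0.2321.
- Time part, the sum of squares of the centred profile (0, 1, r): C = 2(1 − r + r²)/3.
- λ = 40 × S × C / (1 − ρ), with df 4 and 234.

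At r = 1 (fully sustained), C = 2/3. At r = 0 (t1 only, controls fully caught up), C = 2/3. For a t2-only effect, profile (0, 0, 1), C = 2/3. All three give λ = 40 × 0.2321 × 0.6667 / 0.5 = 12.38. The test has the same power for three opposite stories.

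**4. Power of that test, as context.**

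| Share of difference left at t2 | d = 0.55 | d = 0.59 | d = 0.77 |
|---|---|---|---|
| 100% | 74% | 81% | 97% |
| 75% | 64% | 71% | 93% |
| 50% | 60% | 67% | 90% |
| 25% | 64% | 71% | 93% |
| 0% | 74% | 81% | 97% |

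Power dips at partial catch-up, is lowest at 50%, and returns to its starting value at full catch-up, because catching up is itself an interaction.

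**The case against.** **Three occasions in the primary test rests on the abstract alone.** Its wording could simply list when MADRS is rated, and the two-measure sample size points to t0 and t1. This stands. A reader might infer that the primary test is certainly contaminated; the article does not support that. It supports saying that the abstract, the sample size section and the analysis section must be reconciled. An analysis plan not shown here might fix the levels of time, but it would still have to depart from either the abstract or the sample size calculation.

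**The offer is open and the contrast stays randomized.** The Background limits the control definition to the intervention period, so later access is part of the design. The t2 contrast is a valid randomized comparison of two offer strategies. This also stands; what fails is only its reading as a comparison with usual care. Treatment changes are recorded at t1 and t2, and regressions on additional treatment are planned. Adjusting for treatment begun after randomization does not restore the randomized contrast, however. The limitation named in the Discussion concerns other individual treatments, not the trial's own offer.

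**Power.** A reader might infer that the offer leaves the trial underpowered. The figures do not show that: the loss is confined to partial catch-up, and at d = 0.77 power never falls below 90%.

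**Bouldering passes.** A reader might count these as a second route of contamination. They are an alternative to vouchers, those given after t2 cannot affect t2, and nothing in the protocol shows that a pass acts like manualised BPT. The BPT offer is the route that matters.

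**The 1-year strength.** Calling long follow-up a strength is not in itself a claim of superiority over usual care at one year.

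**Conclusion.** The point holds in two parts.

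1. The primary time point is inconsistent: three occasions in the abstract, two in the sample size calculation, and none stated in the analysis section, the hypotheses or Table 1.
2. Whatever the intention was, the t2 contrast is with usual care followed by optional BPT, so it cannot support the stated aim of superiority over treatment as usual.

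If t2 is in the primary omnibus test, a significant result does not distinguish lasting benefit, controls catching up, or a late-only difference. The equal noncentrality depends on the two active arms behaving alike and on equal correlations between occasions. How far the t2 difference shrinks depends on uptake and on the benefit to those who take up BPT, and the protocol gives neither. The core problem is what the result would mean; the power loss is secondary and conditional.

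**What to change.** - State in the abstract, the analysis section and the registry entry that the primary comparison is the group × time interaction on MADRS at t0 and t1 only. This matches the existing calculation, so no extra participants are needed.
- Make MADRS at t2 a secondary outcome, labelled as immediate versus deferred offer of group therapy. Claim no superiority over usual care from it.
- Report how many controls took up BPT after t1, with dates.
- Fix this before any t2 results are seen.

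Cost: a substantive amendment to the registry and protocol of a running trial, and the 12-month result is no longer a primary claim. No added visits are needed. The offer to controls and their rewards can stay as they are; changing the reward partway through four waves would create different control conditions for no clear gain.

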### Data collection

The target variables are being collected with several self-report questionnaires, standardized videoconference interviews, and physical examinations. The secure patient software *Samedi*, which is certified by the German Association of Statutory Health Insurance Physicians (KBV) (DSGVO-compliant), is being used to schedule interviews and examinations as well as to conduct the video interviews. All data are being collected with the web-based data collection system *REDCap2*. Each group is examined before the intervention (t0), again at the end of the 10-week intervention period (t1), and for a third time about 12 months after the end of the intervention (t2). Participants are instructed to answer the questionnaires before their scheduled appointments. The video interviewers are students who are studying either clinical psychology or medicine and have undergone training at the study’s headquarters. The physical examinations, including the blood sampling, are performed before the therapy begins (t0) and again after it ends (t1) by trained students of medicine only.

